## Abstract

Web-based lifestyle interventions have attracted considerable research interest. Available evidence on such interventions suggests health-promoting effects, but further research is needed. Therefore, this study aims to investigate short-, medium-, and long-term health effects of a web-based health program (“TK-HealthCoach”, TK-HC) offered by a national statutory health insurance fund (Techniker Krankenkasse, TK). The study comprises two randomized controlled clinical trials to evaluate the health goals “Increasing Fitness” (F_clin_) and “Losing and Maintaining Weight” (W_clin_). A total of *n* = 186 physically inactive (F_clin_) and *n* = 150 overweight or obese (W_clin_) adults will be randomly assigned to a 12-week interactive (TK-HC) or non-interactive web-based health program using permuted block randomization with a 1:1 allocation ratio. Primary outcomes include cardiorespiratory fitness (F_clin_) and body weight (W_clin_). Secondary outcomes comprise musculoskeletal fitness (F_clin_), physical activity and dietary behavior, anthropometry, blood pressure, blood levels, and vascular health (F_clin_, W_clin_). All outcomes will be measured before and after the 12-week intervention and after a 6- and 12-month follow-up. Additionally, usage behavior data on the health programs will be assessed. Linear mixed models (LMMs) will be used for statistical analysis. Findings of this study will expand the available evidence on web-based lifestyle interventions.

## 1. Introduction

Today’s lifestyle in wealthy societies is increasingly characterized by physical inactivity and unhealthy diets, facilitating the prevalence of overweight and obesity. These lifestyle factors have been identified as global health risks in the latest Global Burden of Disease Study [1]. In 2019, 0.832 million deaths and 15.7 million disability-adjusted life-years (DALYs) were attributed to physical inactivity [2]. Unhealthy diets were blamed for 7.94 million deaths and 188 million DALYs [3], while overweight and obesity contributed to 5.02 million deaths and 160 million DALYs [4]. Particularly for noncommunicable diseases (NCDs), which are a challenging public health problem [5], these behavioral and metabolic risks are among the most modifiable and preventable risk factors [6].

In Germany, 79.5% of women and 75.3% of men are insufficiently physically active, i.e., they do less than 150 min of moderate aerobic activity and muscle-strengthening activities on less than two days per week [7]. They thus do not meet the recommendations for physical activity [8]. Considering current dietary guidelines [9,10], the German population consumes too much fat and protein, especially from animal sources, and too few fruits, vegetables, legumes, and fiber [11]. Moreover, 28.8% of women and 43.3% of men are overweight (body mass index (BMI) ≥ 25.0 kg/m^2^ [12]) and 18.0% of women and 18.3% of men are obese (BMI ≥ 30.0 kg/m^2^ [12]) [13]. Thus, almost half of German women (46.7%) and about two-thirds of German men (61.6%) live with increased body weight [13].

The consequences of these health risks, namely the increased mortality and morbidity risk of NCDs [14,15,16,17], can, however, be countered with the far-reaching potential of a healthy lifestyle promoting physical activity and a healthy diet. There is convincing evidence that these lifestyle factors contribute significantly to the prevention and treatment of many NCDs such as obesity, type 2 diabetes mellitus, and metabolic syndrome [18,19,20,21,22,23,24,25,26,27,28]. Furthermore, it has been shown that they induce positive effects on specific health outcomes associated with these diseases, including anthropometrics [29,30,31], blood pressure [32,33,34], blood glucose [31,35,36], blood lipids [31,36,37], and endothelial function [38,39,40]. Therefore, physical activity, a healthy diet, and normal body weight need to be addressed as essential components of lifestyle interventions for NCDs [41,42].

Most existing lifestyle intervention programs that focus on these components are face-to-face interventions. Their effectiveness in preventing and treating NCDs is already well-proven [43,44,45,46,47]. As a result of progressive digitalization, web-based lifestyle interventions have attracted much attention, mainly because of their accessibility regardless of location or time and comparatively lower costs [48]. Previous research on such interventions indicates a health-promoting potential [49,50,51,52,53,54,55,56,57,58,59]. However, there is still a significant need for further investigations, notably on long-term effects, successful intervention components, and objective health outcomes [60]. Regarding web-based interventions offered by national statutory health insurance funds, most of them refer to unimodal health programs [61,62,63,64] and have rarely been evaluated [65,66,67,68,69]. Based on this state of research, it is evident that web-based lifestyle interventions are still in their infancy and provide considerable research potential. This implies the development of preferably individually tailored, multimodal lifestyle intervention programs and their comprehensive evaluations.

The present study intends to close this gap by evaluating such a program of a national statutory health insurance fund (Techniker Krankenkasse, TK). This program (“TK-HealthCoach”, TK-HC) focuses on sustainable lifestyle changes to prevent NCDs in the long term by offering individually tailored, multimodal health coaching in which individuals can prioritize a personal health goal [70]. The evaluation of this program will be realized as a nationwide study by the scientific direction of the Section of Health Care Research and Rehabilitation Research (SEVERA) of the Medical Center of the University of Freiburg. Therefore, the TK-HC will be evaluated in three randomized controlled online trials (F_online_, W_online_, S_online_) investigating the effects on achieving the health goals “Increasing Fitness”, “Losing and Maintaining Weight”, and “Smoking Cessation” assessed by self-reported outcomes via online questionnaires. The study protocol of these online trials can be found elsewhere [71]. Concerning the health goals “Increasing Fitness” and “Losing and Maintaining Weight”, two additional randomized controlled clinical trials (F_clin_, W_clin_) will be performed to strengthen the effects on health goal achievement by objectively measured health outcomes, such as cardiorespiratory fitness (F_clin_) and body weight (W_clin_), through sports and nutritional medical examinations. For feasibility reasons, these two clinical trials will be conducted only in one specific geographic region of Germany, namely in the southwest of Germany, and will be coordinated by the Department of Sport and Sport Science (DoSS) of the University of Freiburg. This paper outlines the study protocol of these two clinical trials with adherence to the Standard Protocol Items: Recommendations for Interventional Trials (SPIRIT) statement [72,73].

The overall aim of the clinical trials (F_clin_, W_clin_) is to investigate short-, medium-, and long-term health effects of a 12-week interactive web-based health program (TK-HC) compared to a 12-week non-interactive web-based health program in physically inactive (F_clin_) and overweight or obese adults (W_clin_). For this purpose, the effects of each web-based health program on primary and secondary outcomes will first be examined. The hypothesis that participation in each health program is associated with improvements will be tested. Second, the difference between the interactive and non-interactive health program will be examined in terms of their effects on primary and secondary outcomes. The hypothesis will be tested that participation in the interactive health program achieves more significant improvements than participation in the non-interactive one. Finally, the impact of program use on program effectiveness will be examined. The hypothesis that higher frequency and intensity of program use leads to better primary and secondary outcomes in comparison to program use of lower frequency and intensity will be tested.

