#### 2.3.2. Non-Interactive Web-Based Health Program

The program for the control group for both clinical trials (F_clin_, W_clin_) will consist of a simply designed online platform that offers support in increasing physical activity and physical fitness (F_clin_) or losing and maintaining weight (W_clin_) over a 12-week intervention phase. In terms of content, it consists of a health-related knowledge transfer. Thus, only scientific background information on the respective health goal can be found, structured in short articles, but without interactive components. In addition, the user has access to personal data and the study information and consent form for the online and the clinical trial and has the option to withdraw participation from the trials and the health program.

The study participants of the clinical trials (F_clin_, W_clin_) will receive the respective health program after successful baseline assessment. They will log into the program via the project’s landing page. Criteria for discontinuing, interrupting, or modifying the allocated intervention are defined as feeling unwell, worsening health status, illnesses, diseases, injuries, harms, adverse events, or withdrawal from participation. These criteria will be determined by the study participant or the principal medical investigator of the study. Apart from the interventions, the participant will not be allowed to participate in other studies on physical activity or dietary behavior. For successful study participation and to promote adherence, the study participants will get free medical examinations and an activity tracker (Fitbit Charge 3^TM^) [74]. For participating in the online trial, they will obtain a shopping voucher and discount coupons. Apart from that, all study participants will be given free access to the current version of the TK-HC, including all coaching modules after study completion. As the TK-HC was frozen as a study version before the study started, the current version of the TK-HC contains some new content or features as it is continuously developed [71]. To maintain adherence during the study course, the study participants of the clinical trials will be reminded of the medical examinations by telephone and e-mail. To further monitor adherence, usage behavior data on the health programs will be analyzed within the formative evaluation of the online trials [71].

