### 4.3. Statistical Methods

For all analyses, the IBM SPSS Statistics software (Version 28.0.0.0) (IBM Corporation, Armonk, NY, USA) [113] as well as R (Version 4.0.5) [114] and RStudio (Version 1.4.1106) [115] will be used. All primary and secondary outcomes will be assessed on a metric scale level at all measurement time points. Therefore, linear mixed models (LMMs) will be used for statistical analyses of all outcomes. In the repeated measured data, the time points will be nested within cases, so the cases will be the cluster variable. The time points will enter the model as a continuous variable from baseline (0) to the end of the study (3). Random effects for intercept will be estimated. Degrees of freedom will be calculated with Satterthwaite’s method implemented in a specific R package (lmerTest). The basic model will consist of a cross-level interaction and random effects for intercept and slopes.

Level 1:

$Outcome=\beta_{0j}+\beta_{1j}*time+\beta_{nj}*X_{nj}+r_{ij}$

Level 2:

$\beta_{0j}=\gamma_{00}+\gamma_{01}*group+\gamma_{0n}*Z_{0n}+u_{0j}$

$\beta_{1j}=\gamma_{10}+\gamma_{11}*group$ $+u_{1j}$

The cross-level interaction will be between time and the dichotomous group variable (intervention vs. control group). The fixed effect $\gamma_{10}$ will represent the average change over time, while the cross-level interaction $\gamma_{11}$ will represent the difference in change between both study groups. Possible covariates or confounding variables, such as age and gender, can enter the model at the placeholder $X_{nj}$ on level 1 or $Z_{0n}\;$ on level 2.

To analyze short- and medium-term effects, the metric scale time point variable will be changed to a factor variable. Pairwise comparisons will be used with correction for multiple testing to estimate differences between each measurement time point. We will test group differences on time points t1, t2, and t3 as between-group contrast. Within each group, we will compare baseline with program completion (t0 vs. t1) and baseline with follow-up (t0 vs. t2). Additionally, we will contrast program completion with follow-up (t1 vs. t2) and change between follow-up and the end of the study (t2 vs. t3). Moreover, there is no need to account for multiple testing for the two primary outcomes as the two clinical trials (F_clin_, W_clin_) are considered as two independent trials.

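### Change within each arm is to be tested as an effect of that arm's programme, although no arm goes without a programme

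*Protocol article*

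**What the plan says.** The Introduction lists the aims in order. First, "the effects of each web-based health program on primary and secondary outcomes will first be examined", with this test attached: "The hypothesis that participation in each health program is associated with improvements will be tested". Only second comes the randomised comparison, with the hypothesis that "participation in the interactive health program achieves more significant improvements than participation in the non-interactive one".

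Section 4.3 has an analysis for each. For the first aim: "Within each group, we will compare baseline with program completion (t0 vs. t1) and baseline with follow-up (t0 vs. t2"), followed by t1 vs. t2 and t2 vs. t3, with a correction for multiple testing whose method is not named. For the second aim, the model contains a time-by-group interaction (gamma11), and: "We will test group differences on time points t1, t2, and t3 as between-group contrast".

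The comparator is itself a programme. Section 2.3.2 describes it for the fitness trial as "a simply designed online platform that offers support in increasing physical activity and physical fitness", and likewise for losing and maintaining weight. The same section gives free medical examinations and an activity tracker to participants of both arms.

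**The concern.** Change from baseline within one arm measures a programme's effect only if nothing else would have changed the outcome. The protocol itself names several things that could:

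- **Tracker and examinations.** Both arms wear the tracker, with daily data from t0 to t1, keep nutritional protocols and attend four examinations (sections 2.3.2, 2.4.2).
- **Repeat testing, season and weather.** The primary fitness outcome is a 12-minute run on a 400 m track, repeated at four visits, with weather documented (section 2.4.1). Recruitment is planned for January to June (section 2.7), so on schedule t1 falls 12 weeks later in the year than t0.
- **Regression to the mean.** Entry requires activity of at most 60 min/week, or a BMI of 27.5–34.9 kg/m² (section 2.2).
- **Pandemic restrictions.** Section 6 says these could affect the results. They could worsen outcomes as well as improve them.

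Randomisation balances these influences between the arms but does not remove them within an arm. A report that follows the stated aims could therefore credit both programmes with an improvement that neither caused. If the shared drift is unfavourable, it could deny an effect that exists.

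**Working it through.** **1. What each contrast estimates.** Let tau_I and tau_C be the effects of the interactive and non-interactive programmes against no programme, and delta the change common to both arms.

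- Within intervention arm: E(change) = tau_I + delta
- Within control arm: E(change) = tau_C + delta
- Between arms: (tau_I + delta) − (tau_C + delta) = tau_I − tau_C

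Delta cancels only in the third line. With no arm whose expected change is delta alone, neither tau_I nor tau_C can be separated from it.

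**2. The plan's own sample size.** Inputs from section 2.6: d = 0.45 and 0.50, significance level 0.05, power 0.80. A two-sided, two-sample t-test gives 78.49, rounded up to 79, and 63.77, rounded up to 64 per arm. Both match. With 15% dropout, 79/0.85 = 92.9 (stated 93) and 64/0.85 = 75.3 (stated 75). The trials are thus sized on the between-arm comparison.

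**3. How small a within-arm change the plan can declare significant.** Inputs: n = 79 or 64 per arm, and power 0.80. The correction method is not stated; I assume Bonferroni over the 4 listed within-arm contrasts (0.05/4 = 0.0125) up to 8 for both arms together (0.05/8 = 0.00625). A paired t-test approximates the model contrast.

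Normal approximation: dz = (z for 1 − alpha/2 + 0.842)/√n. The exact value uses the noncentral t distribution with n − 1 degrees of freedom.

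| n | alpha | normal approximation | exact dz |
|---|---|---|---|
| 79 | 0.0125 | (2.498 + 0.842)/8.888 = 0.376 | 0.383 |
| 79 | 0.00625 | (2.734 + 0.842)/8.888 = 0.402 | 0.412 |
| 64 | 0.0125 | (2.498 + 0.842)/8 = 0.417 | 0.428 |
| 64 | 0.00625 | (2.734 + 0.842)/8 = 0.447 | 0.461 |

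Without any correction the exact values would be 0.319 and 0.356. Those are too low for this plan, because it does promise a correction.

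**4. The same size in SDs of the outcome itself.** With equal variances at both visits, SD of change = SD × √(2(1 − rho)). The pre-post correlation rho is not in the protocol; I take 0.5 to 0.9.

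| rho | factor | n = 79 | n = 64 |
|---|---|---|---|
| 0.5 | 1.000 | 0.38–0.41 SD | 0.43–0.46 SD |
| 0.8 | 0.632 | 0.24–0.26 SD | 0.27–0.29 SD |
| 0.9 | 0.447 | 0.17–0.18 SD | 0.19–0.21 SD |

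**5. Illustration in natural units.** The SD of change is also not given; I assume 3–5 units.

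- VO2max: 0.383 × 3 = 1.15 to 0.412 × 5 = 2.06 ml/min/kg. By the formula in section 2.4.1 (× 44.73), that is about 51 to 92 m further in 12 minutes.
- Weight: 0.428 × 3 = 1.3 to 0.461 × 5 = 2.3 kg.

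**The case against.** The strongest reply is that effectiveness already rests on the randomised contrast. The overall aim is comparative, a separate between-group hypothesis is stated, gamma11 and the group differences at t1 to t3 are tested, and the sample size is a two-group calculation. The first hypothesis says only that participation is associated with improvement, and no rule declares a programme effective from within-arm change. All of this is true, and it limits the point. It does not remove it: the sentence before the hypothesis speaks of effects of each programme, and that aim has its own tests.

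It can also be said that the biases are possible rather than shown. That stands. The fitness trial selects on activity, not on VO2max, so regression to the mean in its primary outcome is indirect. The weight trial's BMI band is bounded on both sides. The standardised run protocol, fixed time of day and fasting rules reduce some of the noise, though they do not replace a control.

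A reader might infer more than the protocol supports:

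- **That gamma10 is mislabelled.** Section 4.3 says it "will represent the average change over time, while the cross-level interaction" is the difference in change. Under 0/1 coding gamma10 would be the control-arm slope; under −0.5/+0.5 coding it is the average of the two arms. The coding is not stated, and gamma11 is the same under both. This is a reporting clarification, not an error.
- **That change from t0 to t3 is left out.** The named within-group contrasts do not list it, but the main model runs from baseline to the end of study, and pairwise comparisons between the measurement time points are planned.
- **That the main comparison is compromised.** It is not; step 1 shows that the shared drift cancels there.

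**Conclusion.** The point holds for the first aim and its within-arm tests. These cannot show an effect of either programme, because the design has no arm without one. A common change of about 0.38–0.46 SD of the change score would be declared significant in a given arm with 80% power, even after correction. This rests on assumed Bonferroni adjustment over 4 to 8 contrasts, completer numbers of 79 and 64 per arm, and a paired t-test as a stand-in for the model contrast. The conversions to outcome SDs, metres and kilograms rest further on assumed correlations and SDs. Whether such a drift will occur, and in which direction, is not known from the protocol.

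This should be corrected, but it does not threaten the randomised comparison or the sample size. The randomised contrast answers a narrower question: what the interactive programme adds to the non-interactive one. If both helped equally, it would be near zero, and within-arm p-values would not fill that gap.

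**What to change.** 1. In the Introduction, restate the first aim as describing change over time within each arm, and withdraw its hypothesis test.
2. In section 4.3, report within-arm changes descriptively as mean change with 95% CI, including t0 to t3, with no programme-effect claim drawn from them.
3. State that all effectiveness conclusions rest on gamma11 and the group differences at t1, t2 and t3, and concern the interactive against the non-interactive programme.
4. As a clarification only, give the numeric coding of the group variable so that gamma10 can be read unambiguously.

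The cost is a few sentences and one set of within-arm p-values. No data collection, sample size or between-group analysis changes.

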## 2. Materials and Methods: Design, Participants, Interventions, and Outcomes

### 2.1. Study Design, Setting, and Dates

The study is designed in the form of two randomized controlled, parallel-group clinical trials (F_clin_, W_clin_) using permuted block randomization with a 1:1 allocation ratio. As part of nationwide online trials [71], study participants (F_online_, W_online_) from the southwest of Germany (postcode area: 79) will be invited to medical examinations at the DoSS in addition to the online survey. These medical examinations will be carried out before (t0) and after (t1) the 12-week intervention and after a 6- (t2) and 12-month (t3) follow-up. The study is registered at the World Health Organization-approved German Clinical Trials Register (DRKS) (DRKS00020249, date of registration: 11 December 2019).

All interventions will take place online. The health programs were developed as desktop and mobile versions by TK and Vilua Healthcare GmbH (VHG), the project’s IT company. Thus, they will be accessible on electronic devices from anywhere at any time.

The evaluation project was planned and prepared from June 2018 to December 2019, including the implementation of two randomized controlled clinical pilot trials. Data collection started in January 2020 and will be completed by spring 2022.

### 2.2. Eligibility Criteria

For initial trial registration (F_clin_, W_clin_), subjects have to participate in the respective online trial (F_online_, W_online_) and have to live in the southwest of Germany (postcode area: 79). For trial inclusion (F_clin_, W_clin_), male, female, and diverse subjects must be between 18 and 65 years old, predominantly healthy, and willing to be randomized. In case of known health problems or diseases, individuals have to provide a medical certificate from a general practitioner attesting to their ability to participate in the trial and the health program. Specific inclusion criteria for the clinical fitness trial (F_clin_) are defined as a BMI of 18.5–34.9 kg/m^2^ and a physical activity level of ≤60 min/week. Pregnancy is set as an exclusion criterion. For the clinical weight loss trial (W_clin_), subjects with a BMI of 27.5–34.9 kg/m^2^ will be included, and women who are pregnant or breastfeeding will be excluded. Health problems or diseases that partially or entirely exclude the ability to participate in the trial or the health program are exclusion criteria of both clinical trials.

